**Fig. 2 Fig2:**
[figure not shown]
Study design: 1-year course of the study starting with the baseline visit, including clinical characteristics and neuropsychological assessments, food questionnaire, fitness tests, and blood exam for DNA extraction. This is followed by continuous and interim assessments including digital phenotyping and measurement bursts via smartphone, as well as quarterly interim assessments. The study is concluded by a close-out visit after 12 months, repeating some assessments from the baseline visit as well as the food questionnaires and fitness tests

### Primary experimental outcome

Our primary outcome is to test whether the dynamics of affect fluctuation as proposed by the modified DynAffect Model (homebase, affective variability, and attractor strength), differ between ADHD, BD, and BPD, and HC, using within and between measurement burst comparison.

### Secondary experimental outcomes

Owing to the rich dataset, which is generated in our project, and along the basic questions of our project, we investigate several secondary outcomes:

Testing the effect of stress (macro- and micro-stressors) on mood, activity, and sleep;Addressing whether sleep problems precede affect fluctuations, or vice versa;Testing (shared and unique) polygenic risk scores for ADHD, BD, BPD, Depression, neuroticism, and resilience for their effect on mood elation, depression, and affect fluctuation;Finally, by bringing this data together, we will address the question of whether ADHD, BD, and BPD can be conceptualized to lie within a diagnostic spectrum, or whether they are overlapping but comorbid disorders.

### Sample size considerations

To enable a priori power considerations and determine a sufficient number of participants and time points for multilevel modelling, Arend and Schaefer [52] introduced a comprehensive approach using Monte Carlo simulations. Applying the proposed a priori power analyses to our planned study design, with a total of 615 possible prompts per participant over one year (level 1) in 480 individuals (level 2), and medium ICCs of our mood ratings, we estimate the power to detect small to medium effects to be greater than 0.80. These estimates are also in line with Arend and Schäfer’s rule of thumb recommendations for minimal detectable effect sizes [52].

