### Study subjects

To characterize affective variability and to investigate whether it differs between ADHD, BD, and BPD, we will study four groups: (1) adolescent/adult ADHD patients, (2) early course BD patients, (3) young patients suffering from BPD and (4) matched HC, 120 subjects of each group (Table 1).

**Table 1 Tab1:** Numbers of patients to be recruited by each study site:

Disorder	GUF	VHIR	UiB	FBF	UNIGE-HUG	Sum
ADHD	24	24	24	24	24	120
BD	24	24	24	24	24	120
BPD	24	24	24	24	24	120
HC	24	24	24	24	24	120

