### Study workflow

The baseline visit (Table 2; Fig. 2) is the first step of the study. It includes validation of the participant’s already known diagnosis and a detailed assessment of BD, ADHD, and BPD symptoms using validated scales. We will also measure early traumatic life events, impulsivity, sleep, food intake, and fitness level. Additionally, we will collect a blood sample for DNA extraction and genome-wide genotyping. This will provide a comprehensive context for the high-resolution data that we will collect later.

At the baseline visit, the participants will be provided with an app that allows for e-diary assessment and digital phenotyping. This process involves collecting data from their private smartphones, assessing parameters related to communicativeness (such as phone calls and social app usage) and activity patterns (via GPS tracking). Android users will be provided with the app movisensXS (movisens GmbH, Karlsruhe, Germany), and iOS users with m-Path Sense (Katholieke Universiteit Leuven, Netherlands). During five measurement bursts distributed over the year of participation, participants will complete the e-diary on five consecutive days, starting the day after inclusion to the study (see Table 2; Fig. 2). The e-diary sends out prompts following a pseudo-random time-sampling plan at intervals of about 72 min ± 15 min, from 9 h to 21 h. Participants will receive 10 prompts per day.

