The mood assessment items are a reliable tool for the ongoing measurement of temporary emotional states in research using e-diaries [47]. The conceptualization of the momentary affective state includes variation along three dimensions and participants assess their immediate emotional state by rating two opposing items on visual analogue scales for each of the following dimensions: valence (“At this moment I feel”: “content–discontent” and “unwell–well” [reverse coded]), calmness (“agitated–calm” and “relaxed–tense” [reverse coded]), and energetic arousal (“full of energy–without energy” and “tired–awake” [reverse coded]). In addition to mood, we will assess momentary self-esteem with a short form of the Rosenberg Self-Esteem Scale (4 items) [48] that was adapted and established in prior e-diary studies (for example [35]). Further items will assess impulsivity with three items validated by Halvorson et al. [49], positive and negative daily life events (two items), social interactions (two items)), and dysfunctional behavior (two items). During the five-day measurement bursts, participants will also wear wristband activity sensors (move 4, movisens GmbH, Karlsruhe, Germany) to monitor physical activity. Moreover, throughout the 365 days, the participants will complete diaries at the end of the day on mood and sleep (awake or sleepless in bed, time spent asleep during the last 24 h in 1 h segments) (adapted from ChronoRecord, which is a very well validated mood charting system [50, 51]). Once a week, the assessment of the current menstrual cycle will be included in female participants’ end-of-day diary. Each answer will be marked automatically with a time stamp by the e-diary. The prompts were translated to the individual language of the concerning site from English and are displayed for the participants as such (e.g. German for participants of the German site, Italian for the Italian site, etc.).

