### Study limitations

Potential limitations of the study include the small sample size and the drop-out rate due to various protocol violations. We already accounted for these issues and determined measures. To secure participants’ adherence to the study, we will contact them regularly and motivate them to stay on track with the study. The participating sites also guarantee the recruitment structure needed for such a project, as they care for a great number of patients with the investigated disorders and thereby have a great opportunity for the recruitment and supervision of such a study. Patients will benefit from participation in this study by drawing their attention to the occurrence of affective states and therefore enabling them to link their emotions to external and internal events. In the long run, patients will be empowered to detect and cope with emotional dysregulation in a more effective way leading to less symptom burden.

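### The stated power (>0.80 for small to medium effects) is built on pooled totals of 615 prompts and 480 people that do not match the primary group contrasts; for diagnosis and polygenic-score effects the lower part of that range is not supported

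*Protocol article*

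**What the plan says.** Under Sample size considerations, the protocol article refers to a Monte Carlo approach for multilevel models, "with a total of 615 possible prompts per participant over one year (level 1) in 480 individuals (level 2"), assumes medium ICCs for the mood ratings, and concludes: "we estimate the power to detect small to medium effects to be greater than 0.80". It gives no numeric effect size, alpha, ICC value or tested model term.

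Elsewhere the article fixes the following:

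- **Bursts** (Study workflow): "During five measurement bursts distributed over the year of participation, participants will complete the e-diary on five consecutive days". "Participants will receive 10 prompts per day".
- **Evening diary** (Study workflow): "throughout the 365 days, the participants will complete diaries at the end of the day on mood and sleep". It is adapted from a mood-charting system and is not the momentary scale for valence, calmness and energetic arousal used in the bursts.
- **Primary outcome**: homebase, variability and attractor strength compared across ADHD, BD, BPD and HC, "using within and between measurement burst comparison".
- **Groups** (Study subjects): "matched HC, 120 subjects of each group". Table 1 gives these as numbers to be recruited.
- **Hypothesis 1**: BPD and ADHD against BD, on variability and attractor strength.
- **Study limitations**: small sample size and drop-out are named, followed by "We already accounted for these issues and determined measures".

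**The concern.** Diagnosis and polygenic scores vary between people, not within them. Power for such predictors is governed mainly by the number of people in each compared group, and more prompts per person cannot replace people. The power paragraph multiplies the largest prompt count by the largest head count and does not say which contrast it describes.

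This paragraph is the article's only quantitative justification of the sample size. The secondary outcomes include the question whether the three disorders form one spectrum or are distinct but comorbid. If a non-significant difference is read against a stated power above 0.80 reaching down to small effects, it could be taken as evidence of similarity that the design cannot provide.

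**Working it through.** **1. The plan's counts.** 5 bursts × 5 days × 10 prompts = 250. Adding 365 evening diaries gives 615. 4 × 120 = 480. Both totals reproduce.

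**2. The plan's power figure.** It cannot be reproduced, because effect size, alpha, ICC and model term are not given. The checks below assume two-sided alpha 0.05, d = 0.2 as small and d = 0.5 as medium, with d in between-person standard deviations.

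**3. Group contrasts.** The smallest difference detectable with 80% power is approximately (1.960 + 0.842) × √(1/n₁ + 1/n₂). For 120 v 120 this is 2.802 × 0.1291 = 0.362. For 240 v 120 it is 2.802 × 0.1118 = 0.313. The table uses the t distribution, which changes little.

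| Contrast | d for 80% power | Power at d = 0.2 | Power at d = 0.5 |
|---|---|---|---|
| 120 v 120 | 0.36 | 0.34 | 0.97 |
| 240 v 120 | 0.31 | 0.43 | 0.99 |
| 96 v 96 (20% loss assumed) | 0.41 | 0.28 | 0.93 |
| 192 v 96 (20% loss assumed) | 0.35 | 0.36 | 0.98 |

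The article gives no drop-out rate. With 10% or 30% loss, the pairwise detectable d is 0.38 or 0.43. A d of 0.2 would need 393 per group.

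**4. More generous between-person readings at the small end.**
- One-sided, 120 v 120, d = 0.2: 0.46.
- All 480 split 240 v 240, d = 0.2: 0.59.
- Four-group F test with all 480, f = 0.1 (noncentrality 480 × 0.01 = 4.8; df 3 and 476): 0.42. It reaches 0.80 at f of about 0.15.
- Polygenic score as a person-level correlation, r = 0.10, N = 480: atanh(0.10) × √477 = 2.19, so power = Φ(2.19 − 1.96) = 0.59. It reaches 0.80 at r of about 0.13.

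None of these reaches 0.80 at the small end.

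**5. How much the prompt count matters.**
- *Homebase (person mean).* Reliability = ICC/(ICC + (1 − ICC)/m). With an assumed ICC of 0.3 it is 0.996 for m = 615 and 0.991 for m = 250. Scaling d by the square root of reliability, power at d = 0.2 for 120 v 120 is 0.340 against 0.338 (normal approximation).
- *Attractor strength, taken as a lag-1 coefficient.* Standard error = √((1 − φ²)/m). With φ = 0.4 assumed it is 0.037 for m = 615 and 0.058 for m = 250. With an assumed between-person SD of 0.10 to 0.20, reliability falls from 0.88–0.97 to 0.75–0.92. Power at d = 0.35 for 120 v 120 falls from 0.72–0.76 to 0.65–0.74. If only within-day pairs count (25 × 9 = 225), it is 0.64–0.74.

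The shortfall at small effects is therefore already present with 615 prompts. Using 250 adds nothing material for homebase and a moderate loss for attractor strength.

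**The case against.** The best reply is that the article says small *to medium* and gives no number. A detectable d of 0.31 to 0.36 lies between the conventional 0.2 and 0.5, and power at 0.5 is 0.97 or more. This stands for the upper part of the range. It does not help the lower part, which the wording also covers.

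Several stronger readings are tempting, and the documents do not support them:

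- *The stated power is false.* This cannot be shown. With the model term unstated, the figure could be right for a within-person effect, and the secondary outcomes include such aims (stress, sleep and mood).
- *The sums are wrong.* They are correct; the question is what they are used for.
- *Counting 615 instead of 250 prompts causes the shortfall.* Step 5 shows that it does not. Nor does the article bar daily mood from informing homebase, and it plans models for unequally spaced data, so 225 pairs is not a fixed ceiling.
- *480 is the wrong number throughout.* All 480 enter the four-group comparison in the primary outcome. The mismatch is with hypothesis 1, where controls play no part, and with pairwise contrasts.
- *The article contradicts itself on drop-out.* The measures listed under Study limitations are regular contact, motivation and site capacity. These concern retention and recruitment and do not claim an inflated sample. That section also admits the sample is small.

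The full protocol and the simulation set-up are not shown and may hold more detail. The mismatch, however, is between figures printed in this article, so the objection is not about something left out.

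**Conclusion.** The point holds in a limited form. The power statement is computed on totals that do not correspond to the primary between-group comparisons, and for diagnosis or polygenic-score effects it is not supported across the range it names. Before any loss, 80% power begins at a d of about 0.36 pairwise, 0.31 for BPD and ADHD pooled against BD, and r of about 0.13 for a polygenic score. Below those values power drops to roughly 0.34 to 0.59 at conventional small effects.

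These results rest on assumed two-sided alpha 0.05, conventional effect-size labels, no multiplicity adjustment and, except in step 5, perfectly measured person-level parameters. A Bonferroni division by three would raise the pairwise value from 0.36 to 0.42. A reader might infer that the study is too small for its purpose. That does not follow, since medium group differences are well covered.

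**What to change.** Restate the power paragraph without enrolling more participants:

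- Take level 1 as the 250 burst prompts times expected compliance, and level 2 as 120 per group less expected drop-out.
- Rerun the simulation with diagnosis as the person-level predictor of homebase, variability and attractor strength, and state alpha.
- Report the smallest detectable effect separately for the four-group test, for BPD and ADHD against BD, for each pairwise contrast, and for the polygenic scores.
- Limit the claim of power above 0.80 to effects of at least those sizes. If the simulation was of within-person effects, say so and confine the claim to them.

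The cost is one rerun simulation, a reworded paragraph and a less favourable published figure.

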### Statistical methods

To comprehensively analyze the three components of the modified DynAffect Model (home-base, variability, and attractor strength), we will employ established statistical approaches rooted in dynamic systems theory. This includes drawing on the original DynAffect Model [33] or the Affective Ising model proposed by Loossens et al. [39]. Specifically, to differentiate affective dynamics across the three disorders (ADHD, BD, and BPD), and between episodes (manic, depressive, remitted) within our intensive longitudinal data set, we will integrate traditional statistical metrics such as autocorrelation and mean squared successive differences. Furthermore, we will use advanced non-linear models capable of incorporating non-equidistant observations, bimodal distributions (i.e., representing different homebases), and predicting subsequent outcomes influenced by contextual factors (e.g., sleep, stress reactivity, or menstrual cycle) over time [39].

### Genetic analyses

Standard quality control procedures will be undertaken using the PLINK program. Quality control will be implemented first at the marker level, then on the individual level to maximize retention of individuals with valid data (excluding markers with less than 95% complete genotyping, invariant, or with minor allele frequency less than 1%). Hardy Weinberg Equilibrium (HWE) will be tested and controlled for. Heterozygosity and biological relatedness will be quantified using standard procedures in PLINK. Individuals will be excluded if they have genotyping completeness of less than 95%, have ambiguous genetic sex, mismatch between genotypic and phenotypic sex, or have abnormal heterozygosity on autosomes. For analyses of biological relatedness and population structure, the data will be pruned for linkage disequilibrium (LD) to remove redundant SNPs in strong LD (R^2^ > 0.6) with other SNPs and regions with known long-range LD. Biological relatedness will be assessed through identity by descent (IBD) in the LD-pruned dataset in PLINK. Genetic population structure will be mapped using an iterative principal component analysis in PLINK. External reference samples (1000 Genomes) will be used to infer the racial composition of the samples and classify subjects according to genetic heritage. Genomic information on relatedness, ethnicity, and genetic population structure will be used to control for confounding factors.

### Strategies to improve adherence to ema prompts

Improving adherence to EMA prompts in a study focused on mood variations is crucial for obtaining accurate and valuable data. We will use several strategies to enhance adherence, and by this ultimately improving the quality and reliability of data collected in the study.

user-friendly app: we will utilize a user-friendly EMA app that is easy to navigate and provide a seamless experience for participants; we will ensure that the interface is intuitive and visually appealing;positive reinforcement: we will use a system of rewards or incentives to motivate participants, offering small incentives or personalized feedback for consistent participation, which can encourage compliance;clear instructions: we will provide clear and concise instructions on how to respond to prompts and what is expected from participants, ensuring participants understand the purpose and significance of their contributions;training and familiarization: we will offer comprehensive training sessions or tutorials at baseline to help participants become comfortable with the EMA app and its usage;privacy and security: we will assure participants that their data are kept confidential and secure.Missing data: We accounted for the completeness of smartphone data by reviewing it on a regular basis and evaluating the reason for missing data to avoid them in future prompts.

### Dissemination plans

Results of the trial will be published in peer-reviewed scientific journals, with open-access journal being prioritized. Additionally, study results will be presented at national and international scientific conferences. Results will also be disseminated to health care professionals via departmental seminars and to the general public via press and social media.

## Discussion

The present study investigates the dynamics of affect modulation and emotional dysregulation in individuals with ADHD, BPD, and BD. Emotional dysregulation describes difficulties in functional handling of changes in affect and is defined as “excessive expression and experience of emotions with rapid and poorly controlled shift in emotions and abnormal allocation of attention to emotional stimuli” [53]. Intriguingly emotional dysregulation appears transdiagnostically. In case of BPD this is even listed in the diagnostic criteria according to the DSM-V [2], in ADHD and BD this has been proved to be evident as well [53]. Here, ADHD patients showed similar levels of emotional dysregulation compared to BD patients and even higher emotional responsiveness [53].

Even though emotional dysregulation is a transdiagnostic phenomenon and affects a wealth of psychiatric patients, underlying pathomechanisms are not fully understood. From a neurobiological perspective, the brain subcortex represents the basic emotions and sends signals to various brain regions, such as the hippocampus, cingulate cortex, the insular cortex, and the amygdala [54, 55]. The forebrain structures adjust these signals. The balance between glutamate and GABA influences emotional control. The “limbic cerebellum” also participates in emotion dysregulation, and emotion dysregulation may result from congenital defects or later injuries in this area. Emotion Regulation neural circuits involve subgenual and rostral parts of the orbitofrontal, the anterior cingulate, and the dorsomedial prefrontal cortex (PFC), and regions that regulate attentional as well as executive functions, such as the dorsolateral and dorsal anterior cingulate, ventrolateral PFC [54, 56, 57].

The early onset of these disorders and their impact on daily functioning highlights the need for early identification and effective treatment. Understanding the dynamics of affect modulation in these disorders may help identify specific targets for treatment interventions. Additionally, by investigating the similarities and differences in affect regulation across these disorders, we may gain a better understanding of the underlying mechanisms and inform the development of targeted interventions.

### Study limitations

Potential limitations of the study include the small sample size and the drop-out rate due to various protocol violations. We already accounted for these issues and determined measures. To secure participants’ adherence to the study, we will contact them regularly and motivate them to stay on track with the study. The participating sites also guarantee the recruitment structure needed for such a project, as they care for a great number of patients with the investigated disorders and thereby have a great opportunity for the recruitment and supervision of such a study. Patients will benefit from participation in this study by drawing their attention to the occurrence of affective states and therefore enabling them to link their emotions to external and internal events. In the long run, patients will be empowered to detect and cope with emotional dysregulation in a more effective way leading to less symptom burden.

## Data Availability

No datasets were generated or analysed during the current study.

## Abbreviations

AA: Ambulatory Assessment
ADHD: Attention-deficit/hyperactivity disorder
Alda-Scale: Alda Scale for the Assessment of Lithium Response
ASRS: Adult ADHD Self-Report Scale
BD: Bipolar disorder
BPD: Borderline personality disorder
BSL-23: Borderline Symptom List 23
C-SSRS: Columbia-Suicide Severity Rating Scale
CTQ: Childhood Trauma Questionnaire
DERS: Difficulties in Emotion Regulation Scale
DIVA: Diagnostic Interview for ADHD in Adults
FBF: Unit of Epidemiological and Evaluation Psychiatry, Istituto di Ricovero e Cura a Carattere Scientifico (IRCCS)-St. John of God Clinical Research Centre, Brescia, Italy
GAF: Global Assessment of Functioning
GCI-BD: Global Clinical Impression for Bipolar Disorder
GHQ-28: General Health Questionnaire-28
GUF: Department for Psychiatry, Psychosomatic Medicine and Psychotherapy, University Hospital Frankfurt- Goethe University, Germany
IBD: Identity by descent
ICH-GCP: International Conference on Harmonisation - Good Clinical Practice
LD: Linkage disequilibrium
LHC: Life History Calendar
M.I.N.I.: Mini International Neuropsychiatric Interview
MEQ: Morningness-Eveningness Questionnaire
PANAS: Positive and Negative Affect Schedule
PFC: Prefrontal cortex
PRS: Polygenic risk scores
PSS: Perceived Stress Scale
QIDS: Quick Inventory of Depressive Symptomatology
SCID-5-PD: Structured clinical interview for DSM-5 personality disorders
SEM: Structure equation modelling
ST: Steering Committee
TEMPS-A: Temperament Evaluation of Memphis, Pisa, Paris, and San Diego Autoquestionnaire
UiB: University of Bergen and Division of Psychiatry, Haukeland University Hospital
UNIGE-HUG: Department of Psychiatry, Faculty of Medicine, University of Geneva, Geneva, Switzerland; TRE Unit, Division of Psychiatric Specialties, Department of Psychiatry, University Hospital of Geneva, Geneva, Switzerland
UPPS-P: Urgency-Premeditation-Perseverance-Sensation Seeking-Positive Urgency (UPPS-P) impulsive behavior scale
VHIR: Department for Psychiatry, Hospital Universitari Vall d’Hebron, Barcelona, Catalonia, Spain; Group of Psychiatry, Mental Health and Addictions, Vall d’Hebron Research Institute, Barcelona; Biomedical Network Research Centre on Mental Health, Barcelona, Spain
WURS: Wender Utah Rating Scale
YMRS: Young Mania Rating Scale
